##### Secondary outcome measures in included patients

All-cause mortality in included patients. Number of deaths will be collected from national and regional registries [Time Frame: 3 years].Overdose mortality in included patients [Time Frame: 3 years].Retention in naloxone program - number of patients [Time Frame: 3 years].Incidence of witnessing opioid overdoses [Time Frame: 3 years].Incidence in naloxone use and bystander pulmonary resuscitation [Time Frame: 3 years].

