Based on previous studies from other types of settings, one can assume that, during follow-up, 10–20% of those who received naloxone have used these doses [87–89]. It is not possible to establish how many of those given naloxone, in an overdose situation, would have died if the dose had not been administered. It is also not possible to draw conclusions from the literature on how often a person with access to naloxone can be expected to be present when an overdose occurs. With a reduction in number of deaths (per 1000 person years) from 30 to 20 individuals, in regards to the power calculation above, and assuming that only 10% of those receiving naloxone use the dose, 100 (10 × 10) present overdose witnesses are required with access to naloxone for dose to be given in ten cases. With a careful estimate of how often an overdose will be witnessed by someone carrying, or having access to, naloxone, it is our belief that 2000 study participants, with a plan for inclusion of around 1000 patients from OST and 1000 patients from NEP, will be sufficient in order to detect significant reductions in mortality. In addition, the present calculations cautiously assume that the spread of naloxone will take place primarily within the NEP and OST populations. Although the individuals receiving naloxone in the program are either NEP or OST clients, it also should be borne in mind that theoretically, broader groups of individuals at risk of opioid overdoses may benefit from the intervention in case of naloxone spreading outside the core populations seen in the project.

In addition to the effects studied above, the correlation will be calculated between the number of distributed doses in the study cohort and the effects on the outcome variables above.

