### Statistical methods

Comparison of mortality, before and after intervention, is done by Poisson regression with an indicator variable for the intervention (0 = comparison, 1 = intervention), adjusting for age and gender distribution. The effect is described as RR (relative risk), with 95% confidence intervals. *P* values < 0.05 will be considered as statistically significant. The primary outcome measure relates to mortality in the overall cohort. The effect on mortality will be studied in OST and NEP separately, using a subgroup analysis. The evidence in effect between the cohorts will be described by the *p*-value of an interaction test. Outcomes are studied year by year during the intervention period, compared to the comparison period, year by year.

For the study aims regarding the included cohort, this is open, dynamic cohort based on individuals in OST and NEP, where they contribute with person time, as at-risk from entry to study end or death, or by possible exit from the cohort (the earliest of these three events is the end date of the personal time calculation). In the general population analyses, 2013 to 2017 constitute the comparison period, while corresponding data, during 2019–2023, constitutes the intervention period.

Each person included in the follow-up will contribute a record (row) in the research database for each year this person is included in one of the two cohorts. In the row, in addition to each individual’s consecutive number, variables such as date, sex, age, cohort (1 = OST, 2 = NEP), intervention (0 = comparison, 1 = intervention), person time, date in the event of death, and status (alive/dead) at the end of each year, will be registered. In addition, based on public registers of the number of patients in OST, in the analyses it will be possible to control for fluctuations in OST availability (number of patients in methadone and buprenorphine treatment, respectively) in the region, as OST availability is likely to affect mortality rates; for example, based on national register data from the present setting, it has been shown that the risk of overdose mortality varies depending on OST status [90].

Significance, as above, is 5%, when applying a double-sided test. The target for the statistical strength is set at 80% for primary outcome. Secondary outcome and subgroup analyses have not been calculated in strength.

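### The planned dose–outcome correlation uses a raw dose count with no unit or person-time denominator; run as a count correlation on included patients, zero correlation does not mean no naloxone effect

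*Protocol article*

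**What the plan says.** The last paragraph of Power and sample size adds one analysis to the before/after comparison: "the correlation will be calculated between the number of distributed doses in the study cohort and the effects on the outcome variables above". The exposure is a number of doses and the tool is a correlation. No unit (person, clinic, half-year or year), coefficient or denominator is given.

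Secondary outcome measures in included patients words two of the five outcomes as counts: for all-cause mortality, "Number of deaths will be collected from national and regional registries", and then "Retention in naloxone program - number of patients". The other three are overdose mortality, witnessing of overdoses, and naloxone use with resuscitation.

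Statistical methods handles time properly elsewhere. Cohort members are in an open cohort, "where they contribute with person time, as at-risk from entry to study end or death, or by possible exit from the cohort". Each yearly row holds "intervention (0 = comparison, 1 = intervention), person time, date in the event of death, and status (alive/dead) at the end of each year". The mortality comparison "is done by Poisson regression with an indicator variable for the intervention (0 = comparison, 1 = intervention), adjusting for age and gender distribution", with the effect given as a relative risk. The section adds: "Outcomes are studied year by year during the intervention period, compared to the comparison period, year by year". The only exposure term named there is the 0/1 indicator, and doses are not among the example row variables.

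On follow-up, Quantitative data collection gives included subjects 36 months. Recruitment keeps register follow-up running for three years even when a patient stops attending. Refills can happen throughout, for any reason.

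**The concern.** A participant can collect a refill only while alive and attending. Someone who dies in month 10 has had 10 months to collect kits, and a survivor has had 36. Doses and death are therefore negatively associated before naloxone does anything; this is immortal time. The same holds for retention, since staying in the programme is how kits are obtained. When counts are aggregated, both doses and deaths also scale with the number enrolled, which can produce an association in either direction.

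This is the only analysis in the article that relates the amount of naloxone to outcome, in a design with a historical comparison and no concurrent control. The Discussion cites an external dose-related finding. A significant dose correlation would therefore probably be read as support for a causal effect.

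**Working it through.** **The plan's own figures.** The article gives no figure for the correlation. Its stated power can be reproduced, which confirms the mortality inputs used below. Treat person-years as denominators: n1 = 8000, n2 = 3000, rates p1 and p2 = p1 × RR, pooled rate p̄. Then power = Φ[(|p1 − p2| − 1.96·SE0)/SE1], with SE0² = p̄(1 − p̄)(1/n1 + 1/n2) and SE1² = p1(1 − p1)/n1 + p2(1 − p2)/n2.

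- 50/1000, RR 0.75: p̄ = 512.5/11000 = 0.0466, SE0 = 0.00451, SE1 = 0.00424, so Φ(0.86) = 80.6% (stated 81%).
- 30/1000, RR 0.68: 80.4% (stated 81%).
- 30/1000, RR 0.75: 57.0% (stated 57%).

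**Inputs for the no-effect check.** From the article: 2000 participants, 36 months, 30 and 50 deaths per 1000 person-years, two-sided 5%. Assumed: the refill rate g, which is not given. The article expects 10–20% of recipients to use their doses. If that is over three years and only used kits are replaced, g = −ln(0.9)/3 = 0.035 to −ln(0.8)/3 = 0.074 per person-year. Lost and stolen kits are replaced too, so this is a low end, and g up to 0.5 is also shown.

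**Mechanism by hand** (rate 0.03, g = 0.5, fixed three years).
- Probability of death: 1 − e^(−0.09) = 0.086.
- Mean time to death among those who die: 1/0.03 − 3e^(−0.09)/0.086 = 1.48 years.
- Mean kits: survivors 1 + 0.5 × 3 = 2.50; deaths 1 + 0.5 × 1.48 = 1.74. At two doses per kit, 5.0 against 3.5.
- Kit variance is about 1.50, so r = −0.76 × √(0.086 × 0.914)/√1.50 ≈ −0.175 and |r|√2000 ≈ 7.8. Rejection is practically certain.
- At g = 0.035 the same steps give r ≈ −0.047 and |r|√2000 ≈ 2.1, so rejection in a little over half of studies.

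**Simulation, no effect, person level, fixed 36 months** (1000 runs each, kits against death):

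| Deaths/1000 PY | g = 0.035 | 0.07 | 0.2 | 0.5 |
|---|---|---|---|---|
| 30 | 60% | 91% | 100% | 100% |
| 50 | 83% | 98% | 100% | 100% |

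The mean correlation was negative in every cell, and a repeat of the grid gave no rejection with a positive sign.

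**Other ways of carrying out the sentence, still with no effect:**
- Fixed register follow-up, refills ending when attendance ends (assumed exit 0.2/year), 30–50/1000, g 0.035–1: 34% to 100%.
- Uniform staggered entry with a common close, g 0.035–1: 5% to 98% at 30–50/1000; 0.4% to 43% at an assumed 10/1000.
- Staggered entry plus exit, 30–50/1000, g 0.1–2: 5% to 90%.
- 24 units, dose counts against death counts, 10–50/1000: 11% to 35% with equal unit sizes and 60% to 100% with unequal sizes (coefficient of variation 0.3–0.8), r positive.
- Six half-years, cumulative doses against deaths, 30/1000: about 95% with uniform enrolment (mean r about +0.93), 44% with 60% enrolled in the first six months, 7% with all enrolled by then. Under the last two patterns, doses per period against deaths has a mean r of about −0.7.
- Kits against being retained at three years (assumed exit 0.2/year): at least 99%.
- Yearly log relative risks against doses: 4.7% to 5.6%. With three or five points, significance needs |r| above 0.997 or 0.878.

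**Replacement model.** Poisson regression on person-year rows, log person-time offset, doses held as of the start of the row: 4.0% to 6.3% (600 runs per setting, g 0.2–2). A plain correlation on the same rows rejects in 91% to 100%.

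**The case against.** The sentence correlates doses with effects, and Statistical methods describes effects as relative risks studied year by year, with person-time in every row. A reader might infer that the planned analysis ignores person-time and will reject in most trials. The documents do not support that. No unit is stated, no test is tied to this correlation (the 5% level is general), and on the yearly relative-risk reading the error rate is about 5%. The outcomes listed above the sentence also include general-population outcomes, where individual immortal time cannot arise. A condensed article may leave such detail to an analysis plan.

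A reader might also infer that half-year data would show spurious harm. That needs steady enrolment over three years, whereas the Abstract aims to reach a majority within six months and Trial status assumes satisfactory distribution from July 2019.

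These points limit the size and certainty of the finding, but they do not remove it. The article does fix a tool and a raw-count exposure, so this is more than missing detail. The relative-risk reading cannot serve all five included-patient outcomes, because no pre-programme value is described for retention or naloxone use. Where it does apply, it leaves three to five points and almost no information.

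**Conclusion.** The point holds conditionally. As worded, the sentence allows a raw count correlation on included patients, and for that analysis zero correlation is not the no-effect null. At the protocol's 30–50 deaths per 1000 person-years with fixed 36-month follow-up, false rejection is about 60% to 100%, always in the protective direction. This rests on a person-level analysis, a constant death rate, refills unrelated to risk, and assumed refill rates of 0.035 to 0.5 per person-year. Under other schemes the rate runs from below 5% to nearly 100%, and the sign of aggregate count correlations depends on the units and the enrolment pattern. It cannot be said that the planned analysis will mislead, only that the wording permits versions that would. The analysis is supplementary, and the primary comparison is unaffected. The wording should be changed before the cohort outcomes are analysed.

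**What to change.** For included-patient mortality, replace the correlation with the Poisson person-time model in Statistical methods. Add to each row the doses that person had received before the row began. Use log person-time as offset and adjust for time since entry, age, sex and OST/NEP. Report the rate ratio per additional kit with a 95% confidence interval, as supportive only, and state that refills prompted by overdoses can still confound it.

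Do not correlate doses with retention, where the association is built in.

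If an aggregate version is shown, model death rates with a person-time offset against cumulative doses and label it descriptive. Do not use raw counts. Do not correlate doses per person-year with deaths per person-year either: with uniform enrolment and no effect, that rejects in about 25% of studies, because the two ratios share a denominator.

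The cost is a change of wording and one more column in the person-year file. The column should be obtainable from training and refill dates, assuming these are recorded, since questionnaires are completed on both occasions. Precision will be lower than the raw correlation suggests, and doses dispensed within a row count only from the next row.

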### Statistical methods

Comparison of mortality, before and after intervention, is done by Poisson regression with an indicator variable for the intervention (0 = comparison, 1 = intervention), adjusting for age and gender distribution. The effect is described as RR (relative risk), with 95% confidence intervals. *P* values < 0.05 will be considered as statistically significant. The primary outcome measure relates to mortality in the overall cohort. The effect on mortality will be studied in OST and NEP separately, using a subgroup analysis. The evidence in effect between the cohorts will be described by the *p*-value of an interaction test. Outcomes are studied year by year during the intervention period, compared to the comparison period, year by year.

For the study aims regarding the included cohort, this is open, dynamic cohort based on individuals in OST and NEP, where they contribute with person time, as at-risk from entry to study end or death, or by possible exit from the cohort (the earliest of these three events is the end date of the personal time calculation). In the general population analyses, 2013 to 2017 constitute the comparison period, while corresponding data, during 2019–2023, constitutes the intervention period.

Each person included in the follow-up will contribute a record (row) in the research database for each year this person is included in one of the two cohorts. In the row, in addition to each individual’s consecutive number, variables such as date, sex, age, cohort (1 = OST, 2 = NEP), intervention (0 = comparison, 1 = intervention), person time, date in the event of death, and status (alive/dead) at the end of each year, will be registered. In addition, based on public registers of the number of patients in OST, in the analyses it will be possible to control for fluctuations in OST availability (number of patients in methadone and buprenorphine treatment, respectively) in the region, as OST availability is likely to affect mortality rates; for example, based on national register data from the present setting, it has been shown that the risk of overdose mortality varies depending on OST status [90].

Significance, as above, is 5%, when applying a double-sided test. The target for the statistical strength is set at 80% for primary outcome. Secondary outcome and subgroup analyses have not been calculated in strength.

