### Risk factors for overdoses

Recent non-fatal overdose has been shown to represent a marker for increased risk of subsequent fatal overdose [18–20]. Recent period of abstinence, such as post-release from prison [21–24] or inpatient treatment [25–27], polydrug use [28–32], are risk factors highly associated with opioid overdose. Retention in opioid substitution treatment (OST) is associated with reduction of mortality and morbidity [33–39]. However, the OST population in Europe is ageing, with a mean age of death (39.4 years) increasing steadily [1], and carries a high degree of burden when it comes to chronic disease and multi-morbidity [29, 40] which also adds to the risks of overdose. Contrary to many beliefs, tolerant older users have been shown to have a higher risk of death due to overdose than novice users [28, 41].

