## Methods/design

### Setting

The present setting is the county of Skåne, the southernmost county of Sweden with around 1.3 million inhabitants. The major city of the region is the city of Malmö, with around 315,000 inhabitants, and three other major cities (Helsingborg, Lund, and Kristianstad) with populations of 145,000 to 85,000 inhabitants. By Swedish measures, the region of Skåne has unique access to both needle exchange programs (NEP) and opioid substitution treatment (OST) clinics through a network of units which enable reaching a large proportion of illicit drug users at risk of an opioid overdose. The Skåne region has seen a considerable expansion of OST in recent years, and in November 2017, a total of 1514 patients were enrolled in OST in the region. The region has four NEPs, in the four largest cities of the region, and which are open on weekdays and administered by the departments of infectious diseases within the regular hospital system. Altogether, the NEPs of the region have around 1000 to 1100 patients enrolled annually. The number of people at risk of an opioid overdose in the region is likely difficult to establish, as overdoses may occur both to patients known in addiction treatment or harm reduction, based on their opioid dependence, but also to unregular opioid users including patients seen in treatment for other addictive disorders and who may occasionally misuse opioids.

Overdoses in the present region have been examined in several papers during the past decade. For example, it was documented in qualitative interviews that despite an overall willingness from heroin users to help peers who overdose, several potential barriers against adequate interventions by bystanders were identified, such as uncertainty about the victim’s own intentions, the influence of one’s own intoxication, and fear of police when calling the ambulance [81]. Also, a smaller survey carried out in OST patients in the same region demonstrated high prevalence of overdoses, but also a very high interest in participating in a potential naloxone program [78].

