#### Power and sample size

Power has been calculated only for the primary outcome measure. The total population at risk of fatal overdose in the general population is unknown, as people may be at risk of overdose death either because of a severe opioid dependence, a less severe state of dependence or a more unregular use of opioids. As the number of potentially affected individuals is unknown, the power calculations were based on numbers calculated from the number of individuals reached by the intervention at NEP and OST facilities. Thus, power calculations based on the cohort planned to receive distributed naloxone will be considered to be a minimum level with the possibility of a higher effect if the naloxone intervention disseminates also beyond the NEP and OST populations.

The number of patients in OST and NEP is estimated to comprise approximately 2000 individuals, 1000 individuals respectively. Power was calculated based on potential mortality in these two groups (calculated conservatively for 4 years prior to the intervention); a total of 4 × 2000 = 8000 person years; referred to as a ‘comparison period’), and with the conservative assumption that the intervention is calculated to reach the full study group for 1.5 years (intervention group, 2019–2020) (1.5 × 2000 = 3000 person years). The statistical power calculations are made with the Microsoft Excel sheet EPISHEET available for download at www.krothman.org/episheet.xls (downloaded on 14 January 2016).

Assuming that mortality before intervention is 50 deaths per 1000 person years in the overall cohort (that is, a 5% annual risk), a relative risk reduction of 25% (relative risk RR = 0.75) is required in order for the statistical strength to exceed 80% (81%), 5% significance limit, two-sided test, with 8000 person years before intervention (comparison period) and 3000 person years after intervention (intervention group). If however, assuming that mortality before intervention is 30 per 1000 person years in the overall cohort (that is, a 3% annual risk), a higher relative risk reduction, 32% (RR = 0.68), is required for the statistical strength to exceed 80% (81%), 5% significance limit, two-sided test, with 8000 person years before intervention (comparison period) and 3000 person years after intervention (intervention group). If the risk reduction still is 25%, even in this scenario, the statistical strength drops to 57%.

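### The overall OST+NEP cohort model omits the recorded OST/NEP membership, so the pooled RR absorbs any change in mix if the two groups' mortality differs

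*Protocol article*

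**What the plan says.** All references are to the protocol article.

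- **Model.** Statistical methods specifies a before/after Poisson regression with an intervention indicator, "adjusting for age and gender distribution". The effect is an RR with a 95% confidence interval. The section ties the primary outcome measure to the overall cohort.
- **Use of OST/NEP membership.** Each person-year row carries "cohort (1 = OST, 2 = NEP), intervention (0 = comparison, 1 = intervention), person time". Membership is used to analyse OST and NEP separately as subgroups and to give an interaction p-value. It is not named as a covariate in the overall model.
- **The mix can change.** The same section calls the cohort open and dynamic. Setting says "The Skåne region has seen a considerable expansion of OST in recent years, and in November 2017, a total of 1514 patients were enrolled", and puts annual NEP enrolment at 1000 to 1100.
- **Risk is related to OST.** Risk factors for overdoses says "Retention in opioid substitution treatment (OST) is associated with reduction of mortality and morbidity". Statistical methods adds that overdose mortality varies with OST status, and that it will be possible to control for the regional number of OST patients.
- **Planning mix.** Power and sample size says "The number of patients in OST and NEP is estimated to comprise approximately 2000 individuals, 1000 individuals respectively".

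**The concern.** A pooled before/after rate ratio compares two weighted averages of the OST and NEP death rates. The weights are each period's shares of person-time. If the weights move and the two rates differ, the ratio changes even when neither group's mortality has changed. Age and gender terms remove this only so far as they happen to stand in for membership.

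The protocol itself says that risk depends on OST status, that OST was growing and that entry to the cohort is open. It also holds the variable needed for the correction. At stake are bias in the pooled cohort RR, a type I error that departs from the nominal level, and a pooled RR that may disagree with both the OST and the NEP RR.

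**Working it through.** **1. The plan's own power figures.** The inputs are 8000 and 3000 person-years. "Significance, as above, is 5%, when applying a double-sided test", and "The target for the statistical strength is set at 80% for primary outcome". The first scenario reads "Assuming that mortality before intervention is 50 deaths per 1000 person years in the overall cohort", with RR 0.75; the others are 30 per 1000 with RR 0.68 and with RR 0.75. Treating person-years as units in a two-proportion comparison (pooled variance under the null, unpooled under the alternative):

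| Rate per 1000 | RR | Stated power | Recomputed |
|---|---|---|---|
| 50 | 0.75 | 81% | 80.6% |
| 30 | 0.68 | 81% | 80.5% |
| 30 | 0.75 | 57% | 57.0% |

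The figures reproduce. They use one overall rate and an unchanging 1000:1000 cohort, so they make no allowance for a shift in mix.

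**2. Null RR under a shift in mix.** Let s0 and s1 be the OST share of person-time in the comparison and intervention periods, and k the NEP:OST mortality ratio. With no naloxone effect in either group:

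RR = [s1 + (1 − s1)k] / [s0 + (1 − s0)k]

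The protocol gives none of s0, s1 and k, so all three are assumptions. Example with s0 = 0.50, s1 = 0.59, k = 2: (0.59 + 0.82)/(0.50 + 1.00) = 1.41/1.50 = 0.940.

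**3. Type I error.** For a two-sided 5% Wald test on log RR, SE = √(1/D0 + 1/D1), with D0 = rate × 8000 and D1 = rate × RR × 3000. Same example at 50 per 1000: D0 = 400, D1 = 0.05 × 0.940 × 3000 = 141, SE = 0.0979, log(0.940)/SE = −0.63, and the rejection probability is 9.7%.

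| OST share, comparison → intervention | k | Null RR | Type I error at 30 per 1000 | Type I error at 50 per 1000 |
|---|---|---|---|---|
| 50% → 50% | any | 1.00 | 5.0% | 5.0% |
| 50% → 55% | 1.5 | 0.98 | 5.3% | 5.5% |
| 50% → 55% | 2 | 0.97 | 5.8% | 6.4% |
| 50% → 55% | 3 | 0.95 | 6.9% | 8.2% |
| 50% → 59% | 1.5 | 0.96 | 6.0% | 6.7% |
| 50% → 59% | 2 | 0.94 | 7.8% | 9.7% |
| 50% → 59% | 3 | 0.91 | 11.4% | 15.8% |

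If the share moves the other way, from 60% to 50%, the null RR is 1.04, 1.07 and 1.11 for k = 1.5, 2 and 3.

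**4. Where 50% and 59% come from.** 50% is the 1000:1000 planning mix. 59% is 1514/(1514 + 1050), with 1050 the midpoint of the NEP range; the ends of that range give 58% to 60%. This assumes no overlap between the groups. The 1514 is a count from November 2017, inside the 2013–2017 comparison period, so 59% is not an observed intervention-period share. If the share had risen evenly from 50% to 59% over 2013–2017 and then held (assumption), the comparison average would be (50 + 59)/2 = 54.5%. The null RR would then be 0.98, 0.97 and 0.95, with type I error between about 5% and 8%. A shift of about 5 points is therefore at least as reasonable an illustration as 9.

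**5. Effect of adding cohort.** Poisson models were fitted to expected counts at 30 per 1000 with a log person-time offset. With k = 2 and a move from 50% to 60%, the model without cohort gives RR 0.933 (SE of log RR 0.1268). With cohort it gives 1.00 (SE 0.1273). The adjusted RR was 1.00 in every scenario fitted. That follows from holding each group's rate constant over time.

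The calculations leave out age and gender, so these are crude values, not output of the planned model.

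**The case against.** Several objections have force.

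- **The shift is not documented.** This stands. Joining the planning mix to the 2017 count does not give a before/after change, and a point count set against annual enrolment is not a share of person-time. A reader might infer that the mix did move from 50% to 59% and that the RR is biased towards naloxone by a known amount. The documents do not support that.
- **The direction is not settled.** This also stands. The protocol says OST lowers mortality, but it also describes an ageing OST population with heavy multimorbidity that adds to overdose risk. It gives no NEP:OST ratio.
- **This may not be the main result.** A reader might infer that the trial's primary test is biased. Study aims and Primary outcome measures define the primary outcome in the general population of Skåne, 2019–2023 against 2013–2017, where an OST/NEP covariate does not apply. Statistical methods ties the primary outcome to the overall cohort instead, but that conflict does not extend this point to the population comparison.
- **The plan already covers it.** Only in part. The separate OST and NEP analyses are free of the mix shift and would expose it, but they do not correct the pooled RR and are not powered. The control for OST numbers is optional and uses a regional count, which does not replace each person's membership. An interaction model would normally contain a cohort main effect, but the plan does not say that the overall RR comes from that model.
- **An article leaves covariates to the SAP.** The article does state an adjustment set for this model, and membership is not in it.
- **Adjustment does not remove everything.** Correct. If OST expansion draws people from NEP, the risk profile within each group can change, and a cohort term does not correct that.

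**Conclusion.** The point holds as a conditional weakness of the overall-cohort model. The stated adjustment set leaves out a recorded variable that the protocol itself links to mortality, in a cohort whose mix is free to change. Bias requires both a change in mix and unequal mortality; if either is absent there is none.

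The size is hypothetical, because k and both period shares are assumed. The range in the table, a null RR of 0.98 to 0.91, is modest against the planned RRs of 0.75 and 0.68. It is enough to make a pooled cohort RR near the margin hard to interpret. The case for acting rests mainly on the negligible cost of the correction.

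**What to change.** In Statistical methods:

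1. State that the overall-cohort Poisson model includes cohort (OST v NEP) as a covariate alongside age and gender, and that its RR is the overall cohort result.
2. Obtain the interaction p-value by adding the intervention-by-cohort term to that same model.
3. Say which cohort a person-year belongs to when someone attends both programmes.

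The first two steps take a sentence or two and a variable already planned for the database. The model uses one more degree of freedom, and the loss of precision is negligible (SE 0.1268 to 0.1273 in the example). The adjusted RR may look less or more favourable than the unadjusted one, so the choice should be fixed before the data are seen. The change removes bias from the mix between the groups, but not from changes in risk profile within OST or NEP. It leaves the general-population comparison as it is.
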